## 5.4 Unblinding

Participants will be blinded to their treatment allocation. Blinding of surgeons, who administer the medication, and outcome assessors will not be necessary since the co-primary outcomes are patient-reported. Unblinding of patients will be performed on an individual basis as clinical need dictates. All cases of treatment unblinding will be summarised by treatment group (numbers and percentages) together with reasons.

## 5.5 Description of Compliance with Intervention

The trial and control drugs are administered as a single intra-operative dose via peri-articular infiltration. Amount of drug administered will be recorded. As such patient compliance is not relevant to these drugs. If, for any reason, the randomised intervention is not delivered, this will be recorded along with the reason for not receiving the randomised treatment. The instances will be summarised by treatment group as outlined in Table 6. Any differences between the two treatment groups will be explored. In addition, the number of participants experiencing complications during surgery and the total number of complications during surgery will be summarised by treatment group (Table 7), and any differences will be investigated. The types of complications as well as their Clavien-Dindo classification will be summarised.

Summaries will also be provided on time from randomisation to surgery, time in theatre, type of surgery performed and whether this matched the type of surgery planned at randomisation, number of anaesthetists, surgeons and nursing staff present and their grades, ASA grade and anaesthetic used (see Table 7).

**Table 6:** Details of interventions received split by randomised treatment group

|                                                         | Intervention |   | Control |    |
|---------------------------------------------------------|--------------|---|---------|----|
|                                                         | n            | % | n       | %  |
| Received allocated intervention as planned a | X            | X | X       | X  |
| Didn't receive allocated intervention as planned        | X            | X | X       | X  |
| Did not have surgery                                    | X            | X | X       | X  |
| Reason(s) (repeat as needed)                            | X            | X | X       | X  |
| Received alternate trial treatment                      | X            | X | X       | X  |
| Reason(s) (repeat as needed)                            | X            | X | X       | X  |
| Received a non-trial treatment b             | X            | X | X       | X  |
| Reasons(s) (repeat as need)                             | X            | X | X       | X  |
| Did not receive all syringes as planned c    | X            | X | NA      | NA |

a Participants are classed as having received their allocated intervention if for those randomised to Liposomal bupivacaine + bupivacaine hydrochloride all six syringes of Liposomal bupivacaine were administered as planned, and those who were randomised to Bupivacaine hydrochloride only received this

b Details of non-trial treatments will also be provided

c Further details regarding this will be provided in Table 8

**Table 7:** Details of surgery and complications experienced during surgery summarised by treatment group

|                                                                | Intervention | Control |
|----------------------------------------------------------------|--------------|---------|
| Time from randomisation to surgery (days; median, IQR, range)  |              |         |
| Time in theatre (minutes; median, IQR, range)                  |              |         |
| TKR performed (n, %)                                           |              |         |
| Type of surgery different from planned at randomisation (n, %) |              |         |
| Number of anaesthetists present (median, IQR, range)*          |              |         |
| Number of surgeons present (median, IQR, range)*               |              |         |
| Number of nursing staff present (median, IQR, range)*          |              |         |
| ASA Grade (n, %)                                               |              |         |
| Grade I                                                        |              |         |
| Grade II                                                       |              |         |
| Grade III                                                      |              |         |
| Anaesthetic used (n, %)                                        |              |         |
| General                                                        |              |         |
| Neuraxial – spinal                                             |              |         |
| Neuraxial – epidural                                           |              |         |
| Block – femoral                                                |              |         |
| Block – sciatic                                                |              |         |
| Block – adductor canal                                         |              |         |
| Block – lumbar plexus                                          |              |         |
| Patients with complications during surgery (n, %)              |              |         |
| Total no. of complications during surgery (n, %)               |              |         |

\*Further break down by grade will be provided if appropriate.

The process for administering the IMP is more complex than the control. Compliance with this procedure will be summarised (Table 8), as will the surgeon perception of the difficulty of this procedure (Table 9).

**Table 8:** Compliance with the IMP administration procedure for those participants receiving liposomal bupivacaine

|                                                 | Yes |   | No |   |
|-------------------------------------------------|-----|---|----|---|
|                                                 | n   | % | n  | % |
| Syringe 1                                       |     |   |    |   |
| Syringe 2                                       |     |   |    |   |
| Syringe 3                                       |     |   |    |   |
| Syringe 4                                       |     |   |    |   |
| Syringe 5                                       |     |   |    |   |
| Syringe 6                                       |     |   |    |   |
| Injections 14 approx.. 1-1.5ml to intended area |     |   |    |   |
| Tissue visibly expanded with minimal leakage    |     |   |    |   |

**Table 9:** Difficulty of IMP administration for those participants receiving liposomal bupivacaine

|           | n | % |
|-----------|---|---|
| Simple    |   |   |
| Moderate  |   |   |
| Difficult |   |   |

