#### **9.1.1. Name of IMP:**

Liposomal bupivacaine (EXPAREL, Pacira Pharmaceuticals Inc., San Diego, California)

266mg Liposomal bupivacaine will be mixed with 100mg bupivacaine hydrochloride. The volume will then be expanded to 120ml with normal saline and administered as a single dose intra-operatively by periarticular infiltration.

The IMP will be supplied to sites free of charge by Pacira Pharmaceuticals Inc. Initial supplies will be ordered for each site by the Central Study Team following site initiation and confirmation from the Sponsor that all approvals are in place and the site is open to recruitment. For re-ordering of supplies, contact the Central study Team who will arrange further supplies.

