#### **9.1.2. Control:**

Bupivacaine hydrochloride (must be plain, with no adrenaline/epinephrine present)

100mg bupivacaine hydrochloride alone. The volume will then be expanded to 120ml with normal saline and administered as a single dose intra-operatively by periarticular infiltration.

The bupivacaine used in the control arm will not be standardised by brand. The brand used will be what is available to the local participating trusts.

As per standard practice, 100mg Bupivacaine hydrochloride is a flat dose and will not be altered according to BMI in either the intervention or treatment arm.

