### 9.4. Compliance with Trial Treatment

The trial and control drugs are administered as a single intra-operative dose via peri-articular infiltration. As such, patient compliance with the treatment is not relevant in this study. However, surgical compliance with the intervention will be monitored on the Surgery CRF. Each treatment dose will be diluted to the same volume using normal saline as per the manufacturer's instructions. The injection technique of administration will be standardised and compliance with this confirmed on the Surgery CRF. Reasons for any deviation from the administration technique will also be recorded. The amount of drug administered will be recorded.

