### 4.2 Definition of Analysis Populations

Populations for analysis are defined as follows:

Intention to treat (ITT): all participants randomised in their randomised groups.

Per protocol (PP): participants who received the allocated intervention will be analysed according to the treatment they actually received. Participants will be excluded from the PP population if:

- They did not receive the treatment to which they were randomised
- They did not provide sufficient follow-up data for analysis
- They did not satisfy the eligibility criteria for the study

The definition of the PP analysis population will be finalised during a blinded analysis of the data (not separated by treatment group) prior to the final data lock.

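### The SAP judges receipt of treatment by a six-syringe rule in the liposomal arm only, so compliance is not compared like for like and the per-protocol set may inherit the imbalance

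*Combined protocol and SAP*

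**What the plan says.** **SAP, section 5.5.** Footnote a to Table 6 classes patients as having had their allocated intervention if "all six syringes of Liposomal bupivacaine were administered as planned, and those who were randomised to Bupivacaine hydrochloride only received this". The Table 6 row "Did not receive all syringes as planned" has entries for the intervention arm and NA for control. Table 8 is titled "Compliance with the IMP administration procedure for those participants receiving liposomal bupivacaine", and Table 9, on difficulty of administration, is confined to the same patients. The sentence introducing these two tables gives a reason: "The process for administering the IMP is more complex than the control".

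**Protocol, section 9.** For the liposomal mixture, section 9.1.1 says "The volume will then be expanded to 120ml with normal saline". For control, section 9.1.2 says "The volume will then be expanded to 120ml with normal saline and administered as a single dose intra-operatively by periarticular infiltration". Section 9.4 opens by naming both the trial and the control drug. It says that each dose is made up to the same volume and that "The injection technique of administration will be standardised and compliance with this confirmed on the Surgery CRF". Reasons for departing from the technique, and the amount of drug given, are also recorded. Section 9.2 describes six 20 cc syringes for the study drug; its heading refers to the IMP and it does not name the control.

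**Per-protocol population.** SAP section 4.2 builds this set from participants who had the allocated intervention. One ground for exclusion is "They did not receive the treatment to which they were randomised". Syringes and Table 6 are not mentioned, and the definition is to be settled in a blinded analysis before data lock. Protocol section 11.4 had left its full definition to the SAP. Under SAP section 6.4 the per-protocol analysis is a sensitivity analysis for the co-primary outcomes. The primary analysis is by intention to treat (section 6.2).

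**The concern.** An infiltration that stops short of the full set of syringes counts as a failure to receive treatment in one arm and as full receipt in the other. Table 6 would then show more non-receipt under liposomal bupivacaine even if delivery were equally incomplete in both arms. The SAP says that differences between the groups in this table will be explored, so a difference created by the definition could be taken for a finding.

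The per-protocol analysis could inherit the problem. Footnote a is the only place in the SAP that defines receipt of the allocated intervention, and section 4.2 uses nearly the same phrase. If the footnote is carried over, patients with incomplete delivery leave the liposomal arm and stay in the control arm. Incomplete infiltration may go with difficult operations. If those patients also recover worse, the per-protocol comparison would favour liposomal bupivacaine for a reason unrelated to the drug.

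**Working it through.** **1. The plan's own figures.** Six syringes of 20 cc give 6 × 20 = 120 ml, the volume stated for each arm. For the QoR-40 (SAP 3.3: difference 5, SD 15.5, two-sided alpha 0.025, power 90%), n per arm = 2 × 15.5² × (2.241 + 1.282)² / 5² = 239 by the normal approximation and 240 by the t-test. The SAP states 240. Allowing for 4% loss, 240 / 0.96 = 250. These figures reproduce, and the point does not touch them.

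**2. The criteria side by side.**

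| | Liposomal arm | Control arm |
|---|---|---|
| Volume (protocol 9.1) | 120 ml | 120 ml |
| Compliance and amount recorded (protocol 9.4) | yes | yes, on the wording of 9.4 |
| Counted as received (SAP footnote a) | all six syringes as planned | bupivacaine hydrochloride alone received |
| Incomplete-syringe row (SAP Table 6) | reported | NA |

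The stated volumes are equal; the tests of receipt are not.

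**3. Numbers excluded if footnote a governs the per-protocol set.** Let p be the rate of incomplete delivery, taken as equal in both arms. The documents give no rate, so p is an assumption. Of 250 patients per arm:

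- p = 5%: 12.5 liposomal and 0 control patients are excluded. With one rule for both arms, 12.5 and 12.5.
- p = 10%: 25 and 0. With one rule, 25 and 25.

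**4. Shift in the QoR-40 difference.** Let patients with complete delivery have mean m and those with incomplete delivery m − d. The mean of the whole liposomal arm is m − p × d. After exclusion it is m. Control keeps everyone, so the per-protocol difference moves by p × d towards liposomal bupivacaine. The deficit d is also an assumption: 5 points (the target difference) to 15.5 points (one SD). The rejection rate under no true effect uses SE = 15.5 × √(1/n + 1/250), with n = 238 at p = 5% and n = 225 at p = 10%, giving SE of about 1.40 and 1.42.

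| p | d | Shift p × d | Rejection rate (nominal 2.5%) |
|---|---|---|---|
| 5% | 5 | 0.25 | 2.7% |
| 5% | 15.5 | 0.78 | 4.8% |
| 10% | 5 | 0.50 | 3.4% |
| 10% | 15.5 | 1.55 | 12.5% |

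Against the 5-point target, the shift runs from 0.25 / 5 = 5% to 1.55 / 5 = 31%. With d = 0 it is zero for any p. With one rule, and equal rates and deficits in both arms, it cancels.

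**The case against.** The strongest reply is that section 4.2 never invokes footnote a. Its exclusion can be read as wrong treatment or no treatment. Table 6 lists incomplete syringes apart from alternate and non-trial treatment, so a liposomal patient with five syringes could stay in the set. The definition is also still open. This stands: a reader might infer that the per-protocol analysis will exclude patients asymmetrically, but the documents make that possible, not certain.

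Three further inferences are tempting and also go beyond the text.

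- **Identical technique in both arms.** Equal volume is explicit. Section 9.4 supports a standardised technique for both drugs, but section 9.2 does not say that control is given syringe by syringe. Nor do the documents establish that the technique differs and the trial therefore compares drug plus technique. The passages conflict and need to be reconciled.
- **Unblinding of the pre-lock analysis.** Syringe fields filled in for one arm only would reveal allocation. But Tables 8 and 9 limit what is reported, not what is collected, and section 9.4 does not limit the Surgery CRF to one arm.
- **A known bias.** Neither p nor d is in the documents, and the direction depends on the excluded patients doing worse.

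It is also fair that the per-protocol analysis is not the only robustness check. SAP sections 6.2 and 6.3 add a summary-measures AUC and missing-data analyses. None of this repairs the unequal definition in Table 6.

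**Conclusion.** The concern holds in a limited form. As written, Table 6 and footnote a compare treatment receipt by unequal criteria, and the protocol's equal volume and common compliance recording give no basis for that. This rests on the text alone.

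The effect on the per-protocol analysis is conditional. It arises only if section 4.2 is applied through footnote a, if some deliveries are incomplete, and if those patients recover worse. Under the assumed ranges the QoR-40 shift is 0.25 to 1.55 points; at the low end it is negligible. The intention-to-treat primary analysis, the alpha level and the sample size are unaffected. The change should be made before data lock because it is cheap and removes an avoidable source of bias from the compliance table and a planned sensitivity analysis.

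**What to change.** - In footnote a, Table 6 and section 4.2, use one criterion for both arms: allocated drug received, with completeness judged by syringes if these were recorded for control, and otherwise by the amount administered, which protocol 9.4 and SAP 5.5 say is recorded. Alternatively, leave completeness of delivery out of the per-protocol rule in both arms.
- State in section 4.2 which of these applies, and whether incomplete delivery leads to exclusion.
- Report Tables 6 and 8 by arm where the data exist.
- Reconcile the SAP's statement about the complexity of the IMP procedure with protocol sections 9.1 to 9.4.
- If syringe fields prove to be filled in for one arm only, keep them out of the blinded analysis that settles the per-protocol set.

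The cost is a few lines of SAP text and table shells. No new data collection should be assumed. The planned trial period ends on 14 August 2021, 12 months after the last randomisation, which puts the planned end of randomisation at about August 2020, before SAP V2.0 of 17 December 2020. Excluding incomplete delivery in both arms costs a little per-protocol power for the QoR-40: at an assumed 10%, 88.1% (225 against 225) rather than 89.8% (225 against 250), before loss to follow-up.

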## 5.6 Reliability

To ensure consistency, validation checks of the data will be conducted. This will include checking for duplicate records, checking the range of variable values and validating potential outliers by comparing with CRFs and referring back to sites if necessary. Calculations and processes performed by a computer program, including the construction of derived data such as total scores on various outcomes, will be checked by hand calculations (where possible). This check will be conducted for a minimum of 5% of the available data or 20 participants randomly sampled from the dataset. These checks will also confirm whether the data has been imported into the statistical software correctly and will check any merging of different datasets. Clarification will be sought from the trial office in the case of discrepancies.

For each variable, missing value codes will be checked for consistency and the proportion of missing values per variable will be presented. Patterns of missing data will be explored. Where missing data imputation is used, imputed values will also be verified using the validation techniques described above. Sensitivity analyses will be conducted to explore the missing data assumptions used.

## 6. ANALYSIS

### 6.1 Outcome Definitions

The **co-primary outcome measures** in this trial are the Quality of Recovery 40 score and the cumulative daily pain score both measured at 72 hours post-surgery.

Quality of Recovery (QoR) 40 score – a five dimension validated patient reported peri-operative recovery score that has been widely used across a range of surgeries including knee replacement and assesses overall post-operative recovery [19]. It consists of 40 items each of which is graded on a five-point Likert scale. Total scores are calculated by summing the individual items. QoR-40 scores range from 40 (extremely poor quality of recovery) to 200 (excellent quality of recovery) [18]. The primary time point will be 72 hours post-surgery.

This outcome will also be measured at 6, 24 and 48 hours post-surgery and at 6 weeks, 6 and 12 months post-randomisation.

Cumulative daily pain score – pain at rest will be measured using a visual analogue scale (VAS) ranging from 0 (no pain) to 10 (worst possible pain). Measurements taken as close as possible to 6, 24, 48, and 72 hours post-surgery will be included in the primary outcome assessment. This outcome will also be measured at 6 weeks, 6 and 12 months post-randomisation.

The **secondary outcome measures** in this trial are cumulative opiate use, the Oxford Knee Score, the American Knee Society Score, fitness for discharge, and the co-primary outcome measures at additional time points. The health economics outcomes in this trial include summary medication history, EQ-5D-5L, summary healthcare and social services use, and summary employment history.

Cumulative opiate use – all opioids used on evening of surgery (day 0) and days 1, 2, and 3 will be recorded and a running total of cumulative opioid use calculated. A list of acceptable opioids is provided in the trial protocol.

Fitness for discharge – this will be assessed against pre-defined criteria on evening of surgery (day 0) and days 1, 2, and 3 following surgery as per routine clinical care. Patients will be considered fit for discharge when they meet four criteria: (i) ability to mobilise independently; (ii) pain score less than or equal to 3 on a 10 score VAS scale; (iii) ability to straight leg raise; and (iv) ability to bend knee to 90 degrees. It will also be recorded whether patients were discharged, and if they were not discharged when fit for discharge the reasons for this will be collected.

Oxford Knee Score (OKS) – a 12-item patient-reported outcome measure designed to measure pain and function after knee replacement surgery [20]. Each question is scored from 0 (worst outcome) to 4 (best outcome). A total score is obtained by summing across all 12 items to give a single score with a range from 0 (worst outcome) to 48 (best outcome). This outcome will be assessed at 6 weeks, 6 and 12 months post-randomisation.

American Knee Society Score – patient reported outcomes from the AKSS will be collected at baseline, 6 weeks, 6 months and 1 year post-surgery. The AKSS is split into categories where patients record details of satisfaction with treated knee, expectations from their surgery, and ability to perform functional activities. Total scores will be calculated using the scoring manual [21]. The patient satisfaction score composes 5 questions with a maximum score of 40. The patient expectation score composes 3 questions with a maximum score of 15. The functional score is composed of 4 subgroups (walking and standing; standard activities; advanced activities and discretionary activities) with a maximum score of 100. Higher scores indicate better performance. This outcome will be assessed at 6 weeks, 6 and 12 months post-randomisation.

EQ-5D – a validated measure of health-related quality of life consisting of a five dimension health status classification system with 5 response levels (EQ-5D-5L) and a separate visual analogue scale [22, 23]. Responses to the health status classification system will be converted to multi-attribute utility scores, scaled such that 1 is equivalent to perfect health, 0 is equivalent to death, and scores worse than death are possible. The UK value set will be used to generate the EQ-5D-5L index. This outcome will be assessed at 72 hours following surgery, 6 weeks, 6 months and 1 year post-randomisation.

Summary healthcare, social services use and employment history – will be summarised and analysed by the trial health economist. A separate health economics analysis plan will be prepared.

